### Recruitment {15}

Patients will be recruited from renal departments in Denmark by local investigators. To ensure that all incident patients diagnosed with MCN are considered to the study, agreements have been made with the local Pathology Departments to inform the coordinating investigator regularly about new renal biopsies suggesting MCN, allowing this to contact the relevant study site to make sure that all potential participants have been approached.

The first patient in the trial was included in September 2018 with more sites added during 2019 and 2020. The number of included patients is monitored continuously after initiation of the study and targeted efforts will be made to increase recruitment at participating study sites. This will include local analyses to identify any potentially eligible patients not being approached or informed about the study. During the study period, the coordinating investigator will be in personal contact with the local investigators. Study newsletters are regularly distributed to maintain awareness on the trial, and measures will be initiated to minimise any potential, practical obstacles preventing inclusion. If the inclusion of patients in the trial remains insufficient, the number of recruiting sites will be increased by including other renal departments in Scandinavia. Preliminary contact to the Renal Department at Akerhus University Hospital, Oslo, Norway, has been established.

### Assignment of interventions: allocation

#### Sequence generation {16a}

Patients are allocated to the treatment groups at a 1:1 ratio using permuted-block randomisation with random varying block sizes of 4, 6, and 8 stratified by age > 50 years (yes/no). The random allocation list is generated and uploaded to Research Electronic Data Capture (RedCap) by an independent service provider (Clinical Trial Unit, Dept. of Clinical Medicine, Aarhus University) maintaining proper concealment of randomisation.

#### Concealment mechanism {16b}

Randomisation is performed electronically by the local investigator using RedCap.

#### Implementation {16c}

The coordinating investigator and the Good Clinical Practice Unit will visit all trial sites before initiation of the trial to make sure that the local investigators and staff are informed about the protocol, the implementation, and the data management system. The RedCap data management system will be demonstrated, and the relevant access will be provided.

The allocation sequence provided by a RedCap service provider is blinded to all others, but the results of the randomisation are unblinded to both patients and study conductors. After being registered in RedCap at inclusion by the local investigators, the patients are allocated to the intervention according to randomisation.

### Assignment of interventions: blinding

#### Who will be blinded {17a}

The study is an open-label study, and neither the patients nor the investigators will be blinded to the interventions. Baseline data are collected independent of randomisation as it is collected prior to this.

#### Procedure for unblinding if needed {17b}

Not applicable.

### Data collection and management

#### Plans for assessment and collection of outcomes {18a}

The primary outcomes as well as some secondary outcomes are based on blood and urine tests sampled throughout the study period and analysed by using automated and standardised assays by the local Department of Clinical Biochemistry. Patient experienced adverse events are assessed using online questionnaires (SF36 and Cushing QoL) at weeks 2, 6, 10, and 14 before remission, at remission, and at weeks 12, 28, 44, and 52 after remission. Observer assessed, prednisolone-related morbidity is recorded using The Glucocorticoid Toxicity Index [25] reported every 3 months during the follow-up period.

Blood for analyses of genetic variations in the liver enzymes (CYP3A4, CYP3A5, ABCB1, and NR112) will be collected at baseline and stored in a biobank. Unstimulated saliva is sampled after approximately 4 weeks of prednisolone and before dose tapering using a home test (Salivette®). Saliva is sampled five times (0, 2, 6, 12, and 24 h) after taking oral prednisolone. Saliva samples will be stored in the biobank and analysed by liquid chromatography tandem mass spectrometry method in the end of the trial. Concentrations of prednisolone in saliva will be compared to the rate of and time to remission as well as the relapse rate and incidence of adverse events.

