Treatment with prednisolone is associated with important physical and mental adverse effects, including an increased risk of infections, obesity, diabetes, and hypertension and mental changes, e.g. mood changes, depression, and agitation [24], which collectively constitute a strong argument for reducing the cumulative prednisolone dose. Recently, a Glucocorticoid Toxicity Index [25] has been developed to identify and quantitate prednisolone-related complications. The Index includes changes in body mass index, glucose tolerance, blood pressure, lipid status, bone density, steroid myopathy, skin toxicity, neuropsychiatric toxicity, infections, and adrenal insufficiency, as well as gastrointestinal and ocular disease. The Cushing Quality of life (QoL) questionnaire addresses known problem areas in Cushing and is useful for evaluating patient-reported health-related quality of life and correlates with clinical parameters [26, 27]. Also, the short form (SF) 36 is a well-established patient-reported survey that has been used to determine the health-related QoL in the general population and among different groups of patients, e.g. patients with renal disease [28].

The pharmacokinetics of prednisolone are complex. Prednisolone is protein bound, and its metabolism is influenced by gender and plasma albumin as well as by liver function and genetic variations in the enzymes CYP3A4, CYP3A5, ABCB1, and NR112 [29]. Repetitive samplings of non-stimulated saliva provide a good estimate of prednisolone turnover in healthy people [29] and in children with nephrotic syndrome [30]. This may allow for individualised dosing of prednisolone to reduce adverse events without compromising efficacy.

The aim of this study is to test the hypothesis that a new treatment regimen in MCN combining reduced dose prednisolone and active vitamin D is as efficient in inducing remission and has fewer and less severe adverse events than standard prednisolone. Furthermore, we aim to establish models allowing for more personalized medicine based on assessment of the individual’s prednisolone metabolism.

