### Objectives {7}

Based on the potential benefits from reducing cumulative prednisolone dose and the possible positive effects of active vitamin D in nephrotic syndrome, the study will test the following hypothesis:
Treatment of MCN with a reduced dose of prednisolone in combination with active vitamin D is non-inferior to standard dose of prednisolone with respect to rate and time to remission.Treatment of MCN with a reduced dose of prednisolone in combination with active vitamin D reduces the incidence of both the observed and subjective adverse events compared with the standard dose of prednisolone.Patients with MCN and a fast turnover of prednisolone have a lower rate of remission, longer time to remission, and fewer adverse events than patients with a slow turnover of prednisolone.

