#### Intervention description {11a}

Patients will be randomised to either standard treatment with prednisolone 1 mg/kg/day or treatment with prednisolone 0.5 mg/kg/day combined with alfacalcidol 0.5 μg/day. The starting dose will remain unchanged until remission of MCN. After remission, prednisolone will be tapered slowly and discontinued after 25 weeks. All trial sites follow the same tapering regimen. The alfacalcidol dose remains unchanged while the patients receive prednisolone and is discontinued along with prednisolone.

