### Outcomes {12}

Remission is defined by a urine-protein/creatinine ratio < 0.4 g/g and/or a urine-albumin/creatinine ratio < 0.3 g/g on two consecutive tests.

Relapse is defined as the recurrence of proteinuria, i.e. a urine-protein/creatinine ratio > 0.75 g/g and/or urine-albumin/creatinine ratio > 0.5 g/g in two consecutive tests and a decline in p-albumin of > 3 g/l.

Primary endpoints:
Rate of remissions after 16 weeks.Time from diagnosis to remission.

Secondary endpoints:
Rate of relapse within 1 year after remission.Time from remission to relapse.Rate of adverse events and number of hospital admissions.The associations between genetic variations in liver enzyme genes, the concentration of prednisolone in saliva, and remission or relapse.

Safety endpoints:
Patient survivalAcute kidney injury (AKI stage 2 or 3 as defined by KDIGO [31])Serious infections requiring admissionPersistent hypercalcaemia (> 2 weeks) defined by an elevated plasma-ionised-calcium and not normalising by reducing alfacalcidol dose.Severe adverse effects to prednisolone, e.g. gastrointestinal bleeding and severe depression

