### Statistical methods

#### Statistical methods for primary and secondary outcomes {20a}

The primary endpoints are analysed as intention-to-treat. Since this is an open-label study, there is a risk of cross-over between the two intervention groups, but we expect high adherence to intervention groups. Anyway, additional treated-as analyses will be included. Secondary endpoints are analysed as differences in absolute and relative proportions. Factors affecting the primary endpoint (age, baseline eGFR, albuminuria, prednisolone dose or alternative saliva profile) will be identified using a generalised, linear model.

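### Saliva turnover is sampled at about week 4, before a taper that remission itself triggers, so its planned comparison with remission is open to outcome-dependent sampling and reverse causation

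*Protocol article*

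**What the plan says.** The third hypothesis (Objectives {7}) reads: "Patients with MCN and a fast turnover of prednisolone have a lower rate of remission, longer time to remission, and fewer adverse events", compared with slow turnover.

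Turnover is measured by a home saliva test. Plans for assessment and collection of outcomes {18a} states: "Unstimulated saliva is sampled after approximately 4 weeks of prednisolone and before dose tapering using a home test (Salivette". The same section gives the use of the result: "Concentrations of prednisolone in saliva will be compared to the rate of and time to remission as well as the relapse rate and incidence of" (the sentence closes by naming harms as the last outcome). It also places the blood sample for genotyping at baseline.

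Intervention description {11a} ties the taper to the outcome: "The starting dose will remain unchanged until remission of MCN. After remission, prednisolone will be tapered slowly and discontinued after 25 weeks". Trial design {8} says the same.

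Outcomes {12} lists "Time from diagnosis to remission" as a primary endpoint and requires two consecutive tests for remission. Statistical methods {20a} adds: "Factors affecting the primary endpoint (age, baseline eGFR, albuminuria, prednisolone dose or alternative saliva profile) will be identified using a generalised, linear model".

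Background and rationale {6a} says of the drug: "Prednisolone is protein bound, and its metabolism is influenced by gender and plasma albumin", among other factors. Eligibility criteria {10} requires low albumin at diagnosis.

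**The concern.** A predictor should be measured before the outcome it is meant to predict. Here the outcome clock starts at diagnosis and the exposure is measured about four weeks into treatment. Two things can go wrong.

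- **Outcome-dependent sampling.** Whether and when a patient can give a sample that meets both timing conditions depends on when that patient remits.
- **Reverse causation.** If prednisolone metabolism depends on plasma albumin, and albumin recovers as proteinuria resolves, then response can alter the measured turnover that is supposed to explain response. The recovery of albumin is an inference, but Outcomes {12} supports it by making a fall in p-albumin part of the definition of relapse.

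An association between turnover and remission could then appear when turnover has no effect, or a real one could be masked. The article offers this analysis as groundwork for individualised dosing, so a spurious result would matter beyond the trial. The randomised comparison of the two regimens is not affected.

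**Working it through.** **Step 1. Order of events.** Diagnosis starts the outcome clock ({12}). Treatment starts at a constant dose ({11a}). Saliva is taken at about week 4 and before tapering ({18a}). Remission, whenever it comes, starts the taper ({8}, {11a}). A patient who remits and begins tapering before week 4 cannot meet both sampling conditions. The sample is then brought forward to around remission, taken during the taper, or missed. The article does not say which. If the sample is missed, carrying forward the last recorded data ({20c}) has no earlier profile to carry.

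**Step 2. Share in remission by week 4.** The article states no such figure, so there is none to reproduce. Inputs:

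- 80% in remission at 16 weeks on standard treatment (Sample size {14}).
- Two months to remission in adults ({6a}). Reading this as a median *m* is an assumption; *m* = 8 weeks, or 2 × 52/12 = 8.7 weeks.
- Further assumptions: both figures apply to both arms, and time is counted from the start of treatment.

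Formulas for the share F(t):

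- Constant hazard through 80% at week 16: F(4) = 1 − 0.2^(4/16).
- Constant hazard through the median: F(4) = 1 − 0.5^(4/m).
- Weibull through both: F(t) = 1 − exp(−ln 2 · (t/m)^k), with k = ln(ln 5 / ln 2) / ln(16/m). This gives k = 1.215 for m = 8 and k = 1.383 for m = 8.7.
- Linear: 0.8 × 4/16, or 0.5 × 4/m.

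| Curve | In remission by week 4 | Fits both stated figures? |
|---|---|---|
| Constant hazard, 80% at 16 weeks | 33.1% | No: median 16 × ln 2 / ln 5 = 6.9 weeks |
| Constant hazard, m = 8 | 29.3% | No: 75% at week 16 |
| Constant hazard, m = 8.7 | 27.3% | No: 72% at week 16 |
| Weibull, m = 8 | 25.8% | Yes |
| Weibull, m = 8.7 | 21.1% | Yes |
| Linear to 50% at m = 8 or 8.7 | 25.0% or 23.0% | No: 0.5 × 16/m = 100% or 92% at week 16 |
| Linear to 80% at 16 weeks | 20.0% | No: median 16 × 0.5/0.8 = 10 weeks |

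The overall range is about 20% to 33%. Of 96 patients, 0.20 × 96 = 19 to 0.33 × 96 = 32 would be in remission, leaving 77 to 64. The two-test rule lowers the share in confirmed remission.

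**Step 3. What this could do to the analysis.** A simulation took 96 patients whose turnover is unrelated to remission. It used exponential remission times with 21%, 27% or 33% remitted by week 4. Measured turnover was shifted by *d* standard deviations in those already in remission at week 4. Turnover was then correlated (Spearman) with time to remission, censored at week 16, at the nominal 5% level, with 1,500 runs per setting.

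| Assumed shift *d* | False positives, all patients | False positives, only patients not in remission at week 4 |
|---|---|---|
| 0 | 4.5% to 4.9% | 4.1% to 5.8% |
| 0.25 SD | 11.3% to 13.8% | 4.3% to 5.1% |
| 0.5 SD | 27.7% to 44.9% | 4.0% to 5.7% |

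The shifts are assumptions; the article gives none. The table shows how the problem behaves, not how large it is in this trial. The simulated shift occurs only at remission, so partial response before sampling is not covered.

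**The case against.** The sampling sentence can be read more kindly. Week 4 may be a nominal time, with early remitters sampled just before their taper on an unchanged dose, or the sentence may describe two occasions. On the first reading early remitters are still sampled, but at or after remission, so the ordering problem stays. On the second, neither occasion is fixed ahead of response. The readings weaken any claim that these patients go unsampled, and the article does not say that they do.

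The article also does not say that remissions before the sample will be counted. A landmark rule may stand in an analysis plan that is not shown. That is fair. Still, the protocol fixes the sampling time, counts remission from diagnosis and lists the saliva profile beside baseline factors, so following the text as written mixes the order.

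The albumin path is unquantified, and {6a} also says that repeated saliva sampling estimates turnover well in healthy people and in children with nephrotic syndrome. This stands: neither the size nor the direction of a distortion can be judged from the article.

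A reader might infer that the third hypothesis cannot be answered without bias. The documents do not support that. For the 67% to 80% not in remission at week 4 the sample precedes the outcome, and an analysis starting at the sample removes the ordering problem. The hypothesis also covers adverse events, and {18a} adds relapse; relapse and adverse events after the sample are not exposed in this way. Nor is genotype, taken at baseline.

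**Conclusion.** The point holds in limited form. As written, the comparison of saliva turnover with remission and time to remission is open to outcome-dependent sampling and reverse causation. It may concern about 19 to 32 of 96 patients (20% to 33%), fewer if remission must be confirmed. This rests on reading two months as a median, applying the standard-arm 80% to both arms, and an assumed curve.

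A reader might put the share at a quarter to a third. That follows only from constant-hazard curves, each of which misses the other stated figure; the curves through both give 21% to 26%.

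The bias itself has unknown size and direction. The matter is confined to a secondary, association-type analysis.

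**What to change.** For the remission outcomes in the saliva analysis:

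1. Start follow-up at each patient's saliva sampling date (landmark or left-truncated analysis), and include only patients not in remission on that date. State which of the two tests dates the remission.
2. Do not relate a profile to a remission that preceded it.
3. Adjust for the p-albumin nearest the sample where available. Because p-albumin may itself partly reflect response, show the unadjusted result as well. Adjusting for proteinuria at sampling is not advised as a default, since it may lie on the path from turnover to remission.
4. Reconcile Trial design {8}, Intervention description {11a} and Plans for assessment {18a} on what happens to the sample when remission comes before week 4, and report how many patients this affects.

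The cost is analysis wording and one clarification, with no extra samples. The price is that early remitters leave this secondary analysis (about 64 to 77 of 96 remain) and its conclusion is conditional on no remission by the time of sampling. Moving the kit to an earlier date for remaining patients would keep more of them. However, it needs an amendment across sites and splits a small dataset over two sampling times, and the article does not support any particular earlier date.

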#### Plans to promote participant retention and complete follow-up {18b}

Data collected from participants who deviate from the intervention protocol or discontinue from the trial will be analysed and included in data management when relevant unless participant refuses.

### Data management {19}

Data will be collected in an electronic case report file (eCRF) management system RedCap and managed in accordance with regulatory requirements. Only members of the study team (investigators and study nurses) will have access to patient data. The investigators and study nurses are responsible for maintaining the data available for inspection by the regulatory authorities at any time.

### Confidentiality {27}

Personal information about enrolled participants will be stored in the secure RedCap platform, in accordance with authorities’ regulations and General Data Protection Regulation (GDPR). Data potentially shared will be anonymised. Saliva tests and gene samples will be anonymised before analysed by external laboratories.

### Plans for collection, laboratory evaluation, and storage of biological specimens for genetic or molecular analysis in this trial/future use {33}

Standard biochemical analyses (blood and urine) will be performed in the local Department of Clinical Biochemistry using standardised assays with nationally standardised reference intervals. Biological material for research (blood and urine) will be collected, handled and stored at – 80 °C until analysis. Saliva test will be performed by the participants at home and returned by post to The Renal Research Department in Aarhus and stored at − 80 °C until analysed.

### Statistical methods

#### Statistical methods for primary and secondary outcomes {20a}

The primary endpoints are analysed as intention-to-treat. Since this is an open-label study, there is a risk of cross-over between the two intervention groups, but we expect high adherence to intervention groups. Anyway, additional treated-as analyses will be included. Secondary endpoints are analysed as differences in absolute and relative proportions. Factors affecting the primary endpoint (age, baseline eGFR, albuminuria, prednisolone dose or alternative saliva profile) will be identified using a generalised, linear model.

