### Trial design {8}

The trial design is a non-inferior, open-label, randomised, controlled multicentre study including 96 patients with primary, biopsy-proven MCN followed at renal departments in Denmark. The patients are randomised to the following:
Standard prednisolone (1 mg/kg/day, maximum 80 mg/day), orReduced prednisolone (0.5 mg/kg/day) and active vitamin D (alfacalcidol 0.5 μg/day).

When remission is achieved, prednisolone will be taped slowly according to an individual plan (defined by body weight at baseline and the result of randomisation). In both groups, prednisolone will be discontinued 25 weeks after remission. Alfacalcidol will be discontinued at the same time. The patients are followed until first relapse of MCN or for 1 year after remission.

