#### Criteria for discontinuing or modifying allocated interventions {11b}

Prednisolone dose in both arms as well as alfacalcidol dose in the experimental arm may be reduced or discontinued if patients develop severe adverse events to these drugs as assessed by the local investigator. If possible, any deviation from the dosing regimen should be discussed with the sponsor prior to modification. Examples of severe adverse events are hypercalcaemia due to alfacalcidol treatment or psychoses, osteoporotic fracture, development of diabetes, or severe infections during high-dose prednisolone treatment.

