## Discussion

Lower dose of prednisolone in combination with active vitamin D in MCN might be an applicable option for sufficient disease control as a few small randomised studies suggest [14, 32–34].

Patients with MCN and nephrotic syndrome often have no co-morbidities. When being diagnosed with MCN, they experience symptoms such as oedema, fatigue, and foaming urine. After initiating medical treatment, they often experience additional changes and events, which can be related to both the disease and the treatment strategy. Is it imperative that we trace a treatment strategy that is minimising treatment-related adverse events.

This trial uses a predefined electronic randomisation open-labelled design. The open-label design reflects the daily clinically reality. Adherence to treatment strategy and patient compliance will be monitored, e.g. by counting pills. It is commonly anticipated that lower dose of prednisolone decreases adverse events. This might encourage a speedy reduction of prednisolone dose or cross-over from standard to reduced dose of prednisolone especially if the patient prior to treatment has obstacles with e.g. obesity, osteoporosis, hypertension or other known adverse events to prednisolone treatment. Local investigators will be encouraged to adhere to treatment strategy and change in prednisolone dose can only be done after agreement with sponsor or his substitute. The trial will provide evidence to the commonly anticipated belief that the number of adverse events increases with the dose of prednisolone. Alfacalcidol is a well-known treatment among nephrologists and widely used in other patients with chronic nephropathies. Using it in patients with MCN is newfound but expected to be tolerable.

Self-reported, prednisolone associated adverse events have not been systematically evaluated in MCN, but in renal transplant patients, the cumulative dose of prednisolone correlates with reported adverse effects using the Cushing QoL questionnaire [26, 27] and SF36 [35].

This trial should allow us to determine if low dose prednisolone in combination with active vitamin D is clinically as efficient as current standard therapy to induce remission in MCN with the potential to reduce significant adverse events. This may lead to changes of current guidelines for the treatment of MCN. If so, the results potentially can inspire to additional trials in other prednisolone-treated diseases to examine reduced dose of prednisolone.

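### Non-inferiority is to be judged by intention-to-treat with only as-treated support, although the plan acknowledges a risk of cross-over that could dilute a true deficit

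*Protocol article*

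**What the plan says.** Trial design {8} reads: "The trial design is a non-inferior, open-label, randomised, controlled multicentre study including 96 patients". Objectives {7} sets non-inferiority on both the rate of remission and the time to remission.

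Statistical methods {20a} fixes the analysis: "The primary endpoints are analysed as intention-to-treat". On adherence it says "there is a risk of cross-over between the two intervention groups, but we expect high adherence to intervention groups", and then: "Anyway, additional treated-as analyses will be included". It names no per-protocol set and does not require two analyses to agree before non-inferiority is claimed. It also plans a generalised linear model for factors affecting the primary endpoint, with prednisolone dose or saliva profile among them.

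The Discussion gives a direction. Referring to the general belief that a lower dose causes fewer adverse events, it says: "This might encourage a speedy reduction of prednisolone dose or cross-over from standard to reduced dose of prednisolone". It adds that this applies especially to patients who already have problems such as obesity, osteoporosis or hypertension.

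Three further passages bear on the point:

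- Participant retention {18b}: data from participants who deviate or discontinue "will be analysed and included in data management when relevant unless participant refuses".
- Criteria for modifying interventions {11b}: "If possible, any deviation from the dosing regimen should be discussed with the sponsor prior to modification".
- Discussion: "change in prednisolone dose can only be done after agreement with sponsor or his substitute".

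Adherence {11c} says that study medication is counted at each visit and entered in an individual log.

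**The concern.** In a superiority trial, intention-to-treat is usually the cautious choice, because departures from allocation pull the arms together and make a difference harder to show. In a non-inferiority trial the same pull works in favour of the claim. If the reduced regimen induces fewer remissions, each standard-arm patient who moves to the lower dose lowers the control rate and narrows the observed gap.

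The authors saw the problem and chose as-treated analyses as the answer. That analysis groups patients by what they took. By the Discussion's own account, switching would be more likely in patients with particular comorbidities, so the regrouped arms may differ in prognosis. Nor is it clear where some patients would go. Concomitant care {11d} bars active vitamin D as additional treatment, so a standard-arm patient whose prednisolone alone is lowered receives neither randomised regimen.

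The article says that the result may change guidelines, and it plans no interim analysis. The claim will therefore rest on this final analysis.

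**Working it through.** **Inputs from Sample size {14}.** Control remission is 80% at 16 weeks. The margin is 90% of the standard rate, read here as 0.90 × 80% = 72%, which is 8 points. Alpha is 0.05 with sidedness not stated, and 43 patients per group are to complete.

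**Assumptions, because the article gives no figure.** A share c of the standard arm receives the reduced regimen, with c = 10%, 20% or 30%. Each such patient takes on the full reduced-regimen remission rate, and nobody moves the other way.

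**The plan's own figure.** The 43 per group does not follow from these inputs. With equal true rates of 80%, n = (1.645 + 0.842)² × 2 × 0.8 × 0.2 / 0.08² ≈ 309.1, so 310 per group at one-sided 0.05. That is a separate matter. Here 43 is taken as the size that the plan intends.

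**Dilution.** Put the true reduced-regimen rate exactly at the margin, p_T = 0.72. The observed standard-arm rate is then p_C = 0.80 − 0.08c, and the expected intention-to-treat difference is 0.08(1 − c).

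**False non-inferiority rate.** With SE = √{[p_C(1 − p_C) + p_T(1 − p_T)]/43}, the rate is Φ(0.08c/SE − z), where z = 1.645 (one-sided 0.05) or 1.960 (one-sided 0.025).

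Worked case, c = 20%: p_C = 0.784; SE = √[(0.1693 + 0.2016)/43] = 0.0929; 0.016/0.0929 = 0.172; Φ(0.172 − 1.645) = Φ(−1.473) = 7.0%.

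| Assumed cross-over | Expected difference (points) | Rate at one-sided 0.05 | Rate at one-sided 0.025 |
|---|---|---|---|
| 0% | 8.0 | 5.0% | 2.5% |
| 10% | 7.2 | 6.0% | 3.1% |
| 20% | 6.4 | 7.0% | 3.7% |
| 30% | 5.6 | 8.3% | 4.4% |

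If all 96 recruited patients are analysed (48 per arm), little changes. At 20% and one-sided 0.05, SE = √(0.3709/48) = 0.0879 and Φ(0.016/0.0879 − 1.645) = 7.2%.

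**The assumption of full cross-over can err either way.** A switch made part-way dilutes less. A patient who moves to the lower dose without alfacalcidol could, if alfacalcidol helps, do worse than the experimental arm, and then dilution is greater.

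**The two dose-change statements side by side.** {11b}, on severe adverse events, asks for prior discussion with the sponsor where possible. The Discussion makes sponsor agreement a condition of any prednisolone change. The second statement carries no exception for the situation described in the first.

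**The case against.** The strongest objection is that the effect is small and the plan has safeguards. Investigators are to be encouraged to adhere, pills are counted and logged, and the Discussion requires sponsor agreement to prednisolone changes. At 10% cross-over the error moves by about one percentage point. This stands, and it limits the weight of the point.

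Second, a reader might infer that the plan expects cross-over. It does not: {20a} speaks of a risk and expects high adherence, and the Discussion says only that circumstances might encourage it.

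Third, a reader might infer that neither planned analysis could reveal the problem. That goes too far. As-treated moves precisely the patients who switched, and the planned model includes prednisolone dose. What can be said is that neither keeps the randomised comparison, and the direction of any confounding is unknown.

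Fourth, a per-protocol set also selects on events after randomisation and may remove the same kinds of patient. This is true. It is the reason for requiring both sets to agree rather than replacing one with the other.

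Fifth, analysis sets are often left to the SAP, which is not shown and could add a per-protocol set. But the article does not merely stay silent. It raises cross-over and names as-treated as its response, and that stated choice is what is questioned.

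Finally, the qualifier in {18b} might be read as contradicting intention-to-treat or as letting unblinded staff pick patients. The sentence sits under retention, mainly promises inclusion, and does not say who judges relevance. It is loose wording at odds with intention-to-treat, not a proven contradiction.

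**Conclusion.** The point holds in a limited form. The analysis named for an open-label non-inferiority claim can be biased towards that claim by a kind of cross-over that the article itself raises, and its only named support is a non-randomised comparison.

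The bias arises only if the reduced regimen is truly less effective; with equal regimens, switching leaves the expected difference at zero. Its size depends on a cross-over share that the article does not give. Over the assumed range of 10% to 30%, the added error is about 1 to 3 percentage points at one-sided 0.05, and about 0.6 to 1.9 at one-sided 0.025. The calculation covers the 16-week remission rate only. The same narrowing would apply to time to remission but was not quantified.

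This should be corrected, but the documents do not support a claim of gross inflation at the planned size. The difference between {11b} and the Discussion on sponsor agreement is real but secondary, and nothing in the article shows how it would affect the number of deviations.

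**What to change.** - Pre-specify a per-protocol set from the pill counts and medication logs. Fix the adherence rules before the final analysis, including how dose reductions allowed under {11b} are classified. Adjust this analysis for the age stratum and baseline covariates.
- Require the non-inferiority bound to be met in both the intention-to-treat and per-protocol sets.
- Keep as-treated analyses as exploratory, and state how a patient who received neither randomised regimen is grouped.
- Remove the relevance qualifier from {18b}, so that data from all randomised patients enter the intention-to-treat analysis unless consent is withdrawn.
- Reconcile {11b} and the Discussion on sponsor agreement to dose changes. Which rule applies is for the trial team to settle.

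The cost is wording and one more analysis set, with no new data collection. The per-protocol set is smaller and itself open to post-randomisation selection, and a non-inferiority claim becomes somewhat harder to meet.
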